#### Secondary Outcomes of Steps per Day and Energy Expenditure

Secondary outcomes are change in steps per day measured by an accelerometer between randomization and 5 weeks, and in self-reported energy expenditure for walking, and for moderate to vigorous physical activity measured by the French short version International Physical Activity Questionnaire (IPAQ) [52] between randomization, and 5 and 12 weeks. For self-reported energy expenditure, we retained six of the seven items that provided a single continuous score of Metabolic Equivalent of Task (METs)-minutes per week in the last 7 days. The score of energy expenditure for walking is the product of days performed in walking, minutes performed per day, and 3.3 METs. The score of energy expenditure for moderate to vigorous physical activity is the sum of two products: the product of days performed in moderate intensity physical activity (eg, carrying light loads or bicycling at a regular pace), minutes performed per day, and 4.0 METs; and the product of days performed in vigorous intensity physical activity (eg, heavy lifting, or fast bicycling), minutes performed per day, and 8.0 METs. International studies found that the reliability (test-retest) and criterion validity (self-report vs accelerometer data) of the IPAQ generally score around .80 (reliability) and .30 (criterion validity), which is comparable with psychometrics of other self-report physical activity questionnaires [53].

#### Outcomes of Theoretical Variables

Two outcomes assessed only at 5 weeks for Perceived autonomy support (PAS) were drawn from a French version of the Important Other Climate Questionnaire: (1) from a significant other (PAS-SO) and (2) from the intervention (PAS-WEB). These measures assess autonomy support felt from a significant other (PAS-SO) and from either research website visited (PAS-WEB). The two scores are the mean of responses of 6 items for each PAS (significant other [SO] vs intervention [WEB]) rated between “not at all true” (1) and “very true” (7). Higher scores represent greater levels of PAS. Reported Cronbach alphas across three assessments were between .86 and .89 [54].

Self-determined motivation is assessed at baseline and 5 weeks by the French version of the Treatment Self-Regulation Questionnaire. This measure assesses reasons to attain the recommendation of walking 150 minutes per week. We retained the 12 items that assess controlled motivation (6 items) and autonomous motivation (6 items). The two scores are the mean of responses of 6 items for each motivation (controlled vs autonomous) rated between “not at all true” (1) and “very true” (7). Higher scores represent greater levels of controlled and autonomous motivation. Reported Cronbach alphas across four populations were between .73 and .91 for controlled motivation, and between .85 and .93 for autonomous motivation [55].

Perceived competence is assessed at baseline and 5 weeks by the French version Perceived Competence Scale [53]. This measure assesses confidence to attain the recommendation of walking 150 minutes per week. The score is the mean of responses of 4 items rated between “not true at all” (1) and “very true” (7). Higher scores represent greater levels of perceived competence. Reported Cronbach alphas across two assessments were .93 and .96 [54].

Barrier self-efficacy is assessed at baseline and 5 weeks by the French version Barrier Self-Efficacy Scale for cardiac patients [35]. This measure assesses confidence to walk for the recommended 150 minutes per week even if one or more of eight barriers listed are experienced. We retained 8 of the 9 items. The item removed referred to the barrier of experiencing angina or chest pain. Instead of overcoming this barrier, we expect that participants treat the pain and consult a health care professional if the pain is not relieved instead of continuing to increase their walking behavior. The score is the mean of responses of 8 items rated between “(0%) not at all confident” and “(100%) very confident.” Higher scores represent greater levels of barrier self-efficacy. A reported Cronbach alpha was .86 in the original 9-item scale [35].

#### Clinical Outcomes

Quality of life is assessed at baseline and 12 weeks by the French version MacNew Heart Disease Health-related Quality of Life Questionnaire for cardiac patients [28]. The 27 items assess, in the previous 2 weeks, global quality of life and its 3 subdimensions: emotional (14 items), physical (13 items), and social (13 items) [56]. Items include reverse scores and overlap across dimensions. The scores for global quality of life and each dimension are the mean of responses that range between 1 (poor quality of life), and 7 (high quality of life). Reported Cronbach alphas were .94, .94, .89, and .90 in global, emotional, physical, and social respectively [57].

Self-reported 7-day point prevalence smoking status, an accepted norm in assessing smoking status outcomes [58], is assessed at baseline and 12 weeks. The following question is used: “Have you smoked a cigarette, even a puff, in the past 7 days?” (p. 4 [59]), answered with “yes” (0), “no” (1), or “never smoked” (2). Point prevalence assessment had a sensitivity of 96.9% and specificity of 93.4% in detecting dichotomous smoking versus nonsmoking status compared with urinary cotinine [60].

Medication adherence is assessed at baseline and 12 weeks by the Self-Reported Morisky Medication Adherence Scale (MMAS-4) [61]. This measure assesses barriers to cardiac medication use in the previous 2 weeks such as forgetting to take them and stopping them because one feels well. The score is the sum of 4 items rated “no” (0) or “yes” (1) such that lower scores indicate better medication adherence. Scores are dichotomized between medium to low (1 to 4) and high (0). The MMAS-4 had a sensitivity and specificity of 81.0% and 44.0% respectively in predicting controlled blood pressure [61].

Secondary prevention program attendance is measured at 12 weeks by self-report rated by “no” (0) or “yes” (1) of at least one visit, since hospitalization, to a secondary prevention program that offers clinical follow-up with a health care professional for general health, medication adherence, healthy diet, smoking cessation, or exercise. No data on baseline attendance are collected because programs may start 4 weeks or later posthospitalization, which falls around the planned time of randomization.

Data for both emergency department visits and hospitalizations are collected from the medical records at 12 weeks at each study center. For each outcome, one or more emergency department visits or hospitalizations for any reason indicate a score of 1 and no emergency department visits or hospitalizations indicate a score of 0.

Angina frequency is assessed at baseline and 12 weeks by the angina frequency scale of the Seattle Angina Questionnaire. This measure assesses frequency of angina pain and nitroglycerin use that we changed from “in the past 4 weeks” to “in the past 2 weeks.” The score is the sum of responses of 2 items rated between “4 or more times per day” (1) and “none over the past 2 weeks” (6), which is then transformed to score between 0 (worst) and 100 (best). Lower scores represent greater angina frequency. A reported significant positive association was *r*=.31 between greater angina frequency and greater number of refills of sublingual nitroglycerin tablets in the previous year [62].

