### Study Aim and Hypotheses

The aim of this RCT is to evaluate in insufficiently active ACS patients, the effect of a fully automated, Web-based tailored nursing intervention (TAVIE en m@rche) on increased steps per day. Our primary hypothesis is that ACS patients in the experimental group receiving TAVIE en m@rche compared with the control group receiving hyperlinks to publicly available websites will demonstrate a greater increase in change in steps per day between randomization and 12 weeks (H1). Secondary hypotheses are a greater increase in change in steps per day between randomization and 5 weeks (H2), and in energy expenditure for walking and moderate to vigorous physical activity between randomization and 5 weeks, and randomization and 12 weeks (H3 to H6).

We are interested in assessing if the change in SDT variables immediately postintervention at 5 weeks will explain the hypothesized increase in steps per day at 12 weeks. Therefore, we will explore the mediating role of the SDT constructs (perceived autonomy support, controlled and autonomous motivations, perceived competence) and barrier self-efficacy on the effect of TAVIE en m@rche on increased steps per day at 12 weeks (H7 to H11 respectively).

We will also explore the effect of TAVIE en m@rche at 12 weeks on improved quality of life (global, emotional, physical, and social), smoking, medication adherence, secondary prevention program attendance, emergency visits, and hospitalizations (H12 to H20). The potential moderating role of sex on the effect of TAVIE en m@rche on steps per day at 12 weeks will also be explored (H21). Finally, we expect no adverse effect, which is represented by an equal level of angina symptom frequency at 12 weeks in both groups (H22).

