#### Experimental Group

The experimental group receives access to TAVIE en m@rche. The central feature of TAVIE en m@rche is the prerecorded videos of a nurse (see Multimedia Appendix 2) who presents the fully automated tailored intervention content delivered according to patients’ baseline assessments of autonomous motivation, perceived competence, and walking behavior. Other modes of delivery include online text that appears beside the videos to allow simultaneous reading of the video’s content, and downloadable PDF files referred to by the nurse. Access to TAVIE en m@rche starts at randomization between the fourth and fifth week after hospitalization, which depends on when the baseline online assessment is submitted. The suggested completion time of the intervention is 4 weeks but access to the intervention ends at 11 weeks postrandomization. An additional brief “booster” is added at 8 weeks postrandomization. We estimate about 60-75 minutes is sufficient to complete the intervention. TAVIE en m@rche consists of 73 videos, each lasting on average nearly 1 minute with most (n=68) lasting less than 2 minutes. The TAVIE platform has simple webpage layouts and is easy to navigate [41].

The intervention goal is to encourage a progressive increase in walking behavior, up to the recommended 150 minutes per week at moderate intensity, which is determined by an adapted version of the Borg Rating of Perceived Exertion [42]. This walking level is recommended to all patients at discharge for an ACS-related hospitalization by their treating physician unless a contraindication is present such as comorbid physical condition or an environmental constraint. Such patients are ineligible for study participation.

The intervention is based on a theoretical framework that integrates SBNC with SDT. SBNC focuses on nursing values such as fostering a collaborative partnership with the person, supporting the person’s self-determination in their decisions and actions, and working with the person’s strengths in the aim of achieving health and healing. The SDT on human motivation specifies theoretical constructs for physical activity to be targeted by the intervention strategies and to drive the tailoring process. The intervention strategies are specifically targeted toward increasing self-reported perceived autonomy support, autonomous motivation, and/or confidence (combined perceived competence and barrier self-efficacy).

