Interventions (T1) start immediately after allocation to the experimental or control groups. Follow-ups at 5 weeks (T2) and 12 weeks (T3) postrandomization are planned. At both follow-ups, participants in both groups (experimental and control) are sent an email with instructions to wear the accelerometer for 7 days. If participants accept, a brief text message is sent to remind them to read the email. After 7 days of accelerometer wear, a second email is sent to complete the online questionnaires. In addition, at the end of data collection, participants are instructed to return the accelerometer by mail via the prepaid envelope provided. During participation, the first author is available by phone and email to resolve technical difficulties in accessing the intervention or questionnaires.

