### Ethical Considerations

Ethics approval for this multicenter RCT was obtained from the Scientific and Ethics Committee of the Montreal Heart Institute Research Center (reference #MP-33-2015-1887). Procedures follow the mechanism of multicenter studies outlined by the Quebec Ministry of Health and Social Services [67].

We expect that the study population has no additional adverse effects in participating in this RCT because the recommendation for physical activity (ie, walking 150 minutes per week) is consistent with current cardiology practice. Also, past research found that cardiac patients can safely participate in physical activity at home [68,69]. As such, we hypothesize that angina frequency will be equivalent in both groups (experimental vs control).

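### One angina reading at 12 weeks with a 2-week recall is too narrow to stand for no adverse effect: ask the same two items at 5 weeks and limit H22 to the weeks covered

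*Protocol article*

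**What the plan says.** Under Clinical Outcomes, the protocol article says: "Angina frequency is assessed at baseline and 12 weeks by the angina frequency scale of the Seattle Angina Questionnaire". The same paragraph describes the recall period as one "that we changed from “in the past 4 weeks” to “in the past 2 weeks". Table 2 agrees: the angina row is marked at baseline and 12 weeks and is blank at 5 weeks.

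Study Aim and Hypotheses gives this measure its role: "we expect no adverse effect, which is represented by an equal level of angina symptom frequency at 12 weeks in both groups (H22"). Ethical Considerations repeats the claim without a time point: "we hypothesize that angina frequency will be equivalent in both groups (experimental vs control").

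On timing, the Experimental Group section says: "The suggested completion time of the intervention is 4 weeks but access to the intervention ends at 11 weeks postrandomization". It adds: "An additional brief “booster” is added at 8 weeks postrandomization". Timeline and Procedures says: "Follow-ups at 5 weeks (T2) and 12 weeks (T3) postrandomization are planned". At each follow-up an email first starts the accelerometer week, and then: "After 7 days of accelerometer wear, a second email is sent to complete the online questionnaires".

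**The concern.** Angina frequency is the only measure the article names as representing harm. If raising walking provokes angina, some of it would be expected while walking is first being raised. The one follow-up reading comes late and looks back only 2 weeks.

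The article itself describes how early angina could have gone by then. In explaining why the angina item was dropped from the barrier self-efficacy scale, it expects participants with chest pain to treat it, and to seek care if it persists, rather than go on increasing their walking. The experimental program also asks participants who report exercise intolerance to hold off and come back two weeks later. Someone who has angina in the early weeks and responds in this way can truthfully report none over the last 2 weeks at week 12.

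The risk is that H22 leans toward reassurance: similar scores late in follow-up could be reported as no adverse effect, although the early weeks gave no angina-frequency data in either arm.

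**Working it through.** No sample-size or power figure is involved. The check places the recall windows on the post-randomization time axis.

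**Inputs**
- Recall length: 2 weeks (Clinical Outcomes).
- Follow-ups: weeks 5 and 12 (Timeline and Procedures).
- Questionnaire: sent after 7 days of wear. The article does not fix whether the wear week ends or begins at the nominal week, so both cases are shown.
- Suggested completion of the web content: weeks 0-4. Booster week: 8-9 (Experimental Group).

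**Formula.** A questionnaire answered at week t covers t − 2 to t. Coverage is the overlap with weeks 0-12, divided by 12. The baseline reading precedes randomization and adds nothing.

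| Schedule | Windows (weeks) | Of weeks 0-12 | Of weeks 0-4 | Booster week 8-9 |
|---|---|---|---|---|
| As written, answered at week 12 | 10-12 | 2/12 = 17% | 0 | no |
| As written, answered one week later | 11-13 | 1/12 = 8% | 0 | no |
| 5-week reading added, answered at weeks 5 and 12 | 3-5 and 10-12 | (2 + 2)/12 = 33% | 1 | no |
| 5-week reading added, each answered one week later | 4-6 and 11-13 | (2 + 1)/12 = 25% | 0 | no |

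As written, about weeks 0-10 (or 0-11) have no between-arm angina-frequency data.

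**Role of the recall length.** With the instrument's 4-week recall at both follow-ups, the windows would be 1-5 and 8-12 (8 of 12 weeks, 3 of the first 4, booster week included). Answered one week later, they would be 2-6 and 9-13 (7 of 12 weeks, 2 of the first 4, booster week missed). So the shortened recall contributes to the gap as well as the missing visit.

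**Burden.** From Table 2, the 5-week questionnaire has 7 + 6 + 6 + 12 + 4 + 8 = 43 items. Adding two makes 45.

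**The case against.** Five points can be made for the plan.

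**Walking, not website access, is the exposure.** The 4 weeks are a suggested completion time for content that takes about 60-75 minutes. The walking goal has no stated end at week 4, and H1 expects extra steps to be present at 12 weeks. If the intervention works, the 12-week angina reading falls while the added walking is still under way. This stands. A reader might infer that the whole exposure went unobserved because the reading misses the suggested completion period and most or all of the access period. The article does not support that inference. What remains is angina that comes early, passes, or makes the participant walk less.

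**Other data exist.** Emergency visits and hospitalizations are collected in both arms at 12 weeks, so it would be wrong to say that angina in the early weeks is never observed. But each is scored yes/no for any reason, is taken from study-center records, and is listed among the expected improvements (H12 to H20). They would count severe episodes only and cannot be attributed to angina. The login question on exercise intolerance is in the experimental arm only, serves tailoring, and is not an outcome, so it gives no comparison between arms.

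**H22 and its measure agree.** H22 is worded for 12 weeks, so there is no contradiction. The overreach lies in letting that reading represent no adverse effect, and in the Ethical Considerations sentence, which has no time point.

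**This is a journal article.** Adverse-event recording may be set out in a fuller protocol. Nothing can be concluded about it, and this point does not say that it is missing.

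**The shorter recall may have had a reason.** It may have been meant to keep the baseline reading clear of the hospital stay. The article does not say so, and this would not explain leaving the scale out at 5 weeks.

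**Conclusion.** The point holds in a limited form. One 2-week window near the end of follow-up, covering 1-2 of 12 weeks (8-17%), is too little to represent no adverse effect. Early or transient angina can be missed, and the error leans toward reassurance. How much would be missed cannot be estimated, because the article gives no angina rates.

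Adding the scale at 5 weeks helps but does not close the gap. It gives 3-4 of 12 weeks (25-33%), at most 1 of the first 4 weeks, and nothing around the booster. The upper figure applies only if questionnaires are answered at the nominal week. The 7-day wear delay affects week 5 just as it affects week 12, which is why a range is given. The wording change is therefore needed as well.

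This is an inexpensive improvement to the safety statement. It does not touch the primary outcome or the sample size.

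**What to change.** 1. Add the existing two-item angina scale, with the same 2-week wording as at baseline, to the 5-week online questionnaire in both arms, and mark it in Table 2.
2. Report the between-arm difference in angina frequency at 5 and at 12 weeks.
3. Reword H22 and the matching sentence in Ethical Considerations to claim only similar angina frequency in the weeks covered by the recall, not absence of adverse effect over the trial.

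Keeping the 2-week wording makes the 5-week values comparable with baseline and 12 weeks.

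**Cost.** Two items are added to a 43-item questionnaire that both arms already receive. This is about one minute per participant (an estimate) plus a small amendment. Recruitment began in March 2016, so participants already past week 5 would have no 5-week value. The rewording in step 3 needs no new data and applies to the whole trial.

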#### Sociodemographic and Clinical Data

At recruitment in hospital (-T2), sociodemographic and clinical data are collected. Nine items in a paper-based self-report questionnaire assess employment, education, marital status, and other demographics. Other data including medical history, diagnosis, laboratory tests, in-hospital events, cardiac risk factors, intermittent claudication, and documented referral to a secondary prevention program are collected from the medical chart after hospitalization. Also, depressive symptoms are assessed at recruitment (-T2) by the 9-item French version Patient Health Questionnaire (PHQ-9). The PHQ-9 administered at recruitment in hospital allowed us to refer participants with abnormal scores to the treating cardiologist. At baseline (-T1), fatigue is measured by the 7-item short form French version [63]. Based on our literature review prior to commencing our RCT, depression and fatigue were retained as potential covariates rather than outcome variables because of the uncertainty that Web-based interventions in ACS populations can decrease depression symptoms [28] and because it is unknown if such interventions can decrease fatigue as this variable has not been previously tested in the Web-based ACS literature.

#### Intervention Adherence

During the intervention (T1), intervention adherence data are collected. For TAVIE en m@rche, data are collected on the number of times videos and webpages are viewed and documents are downloaded. Time spent in the intervention will be estimated from these data. For the control group website, data on the number of website visits per person are collected by Google Analytics. Because the control group is provided a single webpage of hyperlinks of publicly available websites, collecting data from these websites is not possible.

### Statistical Methods

The Montreal Health Innovations Coordinating Center provided expertise for the statistical methods. Baseline characteristics will be compared using descriptive statistics to identify trends in group imbalances, and the analyses will be consistent with intention-to-treat principles, in which data at a given time point will not be excluded from the analysis [64]. Missing data will be examined and handled according to best practice in that field [65].

For the analyses of single continuous variables (eg, the primary outcome of change in steps per day), repeated measures analysis of covariance models will be used with covariates that include gender, age, diabetes, intermittent claudication, baseline smoking status, depression symptoms, and fatigue. For analyses of multiple continuous variables (eg, the secondary outcomes of change in walking and moderate to vigorous physical activity), repeated measures multivariate analysis of covariance models will be used with the same covariates as the above model. For single dichotomous variables with baseline values (eg, smoking status), sequential logistic regression models will be used. For single dichotomous variables without baseline values (eg, hospitalizations), chi-square models will be used. A mediation analysis will use a sequence of one-way analysis of variance models with Bonferroni adjustments, in which the alpha will be divided by the number of tests performed. Adjusted and unadjusted means or proportions in each group (experimental and control) will be provided along with a 95% confidence interval. No adjustments in *P* values will be made for the hypotheses on secondary and tertiary outcomes because these are aimed at supporting the primary hypothesis on steps per day rather than claiming intervention effect [66].

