	**Clinical data**									
		Emergency visits and hospitalizations		N/A						x

Recruitment (-T2) takes place in-hospital. Potential participants are identified through patient lists during hospitalization, and we then proceed with preliminary eligibility screening using patients’ medical charts (Figure 2). Eligibility screening, rather than being based on a 24-hour and 7-day a week schedule, is based on the recruiters’ irregular schedules, which vary depending on their availability to present at one of the four sites or on other constraints such as work (academic or other) unrelated to recruiting. When potential participants are approached in hospital, eligibility is confirmed (ie, inclusion/exclusion based on in-person interview), and the study protocol is explained. After signed consent is obtained, self-administered paper questionnaires on sociodemographic data and depressive symptoms are completed. Participants are then given an accelerometer and an open prepaid envelope to use when sending it back to the researcher at the end of the study. After hospital discharge, clinical data are collected from the medical chart.

Baseline (-T1) is at the beginning of the third week posthospital discharge. In conjunction with an email, participants are contacted by phone to confirm their willingness to participate. This email includes a hyperlink to download and install the software into the participants’ computers, allowing the accelerometer data to be synced to the company’s server. Thereafter, the data can then be downloaded into the researcher’s computer. During the same phone call, participants are instructed to wear the accelerometer daily for 7 days from awakening to bedtime. After 7 days of accelerometer wear, a second email is sent that includes a hyperlink to access the first online questionnaire. Although we expect most participants to complete the baseline accelerometer wear followed by the online questionnaire within 1 week, a maximum window of 2 weeks is allowed to complete baseline assessments.

Randomization (T0) and allocation to the experimental or control groups occur upon submission of the baseline questionnaire at the fourth or fifth week posthospital discharge, allowing participants the window of 2 weeks to complete baseline assessments. Each participant receives, by automated email from the TAVIE platform, access to either TAVIE en m@rche or the control group involving publicly available websites.

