### Sample Size Calculation

To detect a difference in change between randomization and 12 weeks of 1500 steps per day (SD 2824) in favor of the experimental group compared with the control group, a total of 148 participants (n=74 participants per group [57 plus 17 for attrition], and n=37 per recruitment center) is needed, given a two-sided 5% significance level, power of 80%, and an expected attrition of 23%. The 1500 steps per day is an approximation of half of the recommended daily minutes of moderate intensity physical activity [47]. The attrition of 23% was reported in a meta-analysis of Web-based interventions, in which the experimental groups had an average intervention duration of 13 weeks [17]. The SD of 2824 steps per day was estimated using data found in an RCT of a counseling intervention in ACS patients in Quebec [48].

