### Randomization and Allocation

Randomization is planned by an offsite coordinating center. It is stratified by study center to help protect against between group imbalances if recruitment differs in one or more study centers [49]. Per stratum, random numbers are given for each assignment. Random assignments follow a 1:1 allocation using random block sizes determined by the coordinating center to minimize the chance of group imbalances [49].

The assignment sent by the coordinating center in electronic list (.xls) format was uploaded in the TAVIE platform. The allocation sequence is concealed. Upon submission of the baseline questionnaire, the TAVIE platform sends an automated email of the assignment to the participant. This email includes the hyperlink and password to access the experimental TAVIE en m@rche or to receive a different hyperlink to access the control of publicly available websites.

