### Outcomes

#### Primary Outcome of Steps per Day

The primary outcome is change in steps per day measured by an accelerometer between randomization and 12 weeks. We chose 12 weeks as the primary endpoint rather than 5 weeks to assess the persistence of steps performed beyond the end of the intervention’s 4-week period. The accelerometer step count data are concealed, uploaded wirelessly to a server [50], and downloaded in the first author’s computer. Similar to step counts measured by a previously validated pedometer, step counts measured by the accelerometer worn on a shoe had less than 2% error compared with observed step counts measured by hand tally counter [50]. Participants are instructed to clip the accelerometer on one of their shoes during waking hours. If they are not wearing shoes, they are then instructed to clip it at their waistline clothing (belt or pants) as recommended by the manufacturer.

The steps per day mean will be estimated using ≥3 valid step-days within the 7-day wear period, which is an accepted norm in adult populations [51]. A valid step-day will be determined by a wear time of ≥10 hours per day [51]. Fewer than 3 valid step-days will be treated as missing data.

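### Baseline steps per day is not among the covariates named for the primary model, so the treatment contrast as written is valid but less precise than the planned data allow

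*Protocol article*

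**What the plan says.** The section on the primary outcome states: "The primary outcome is change in steps per day measured by an accelerometer between randomization and 12 weeks". Statistical Methods assigns single continuous outcomes, with this one as the example, to repeated measures analysis of covariance with "covariates that include gender, age, diabetes, intermittent claudication, baseline smoking status, depression symptoms, and fatigue". Baseline smoking is in that list; baseline steps is not. The abstract gives a shorter list (sex, age, fatigue, depression symptoms), also without baseline steps. Both lists are worded as examples or inclusions rather than as complete.

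The baseline measurement is planned for every participant. Under Timeline and Procedures, before randomization, "participants are instructed to wear the accelerometer daily for 7 days from awakening to bedtime", and Table 2 marks steps per day at baseline, 5 weeks and 12 weeks.

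The Sample Size Calculation is framed on change: "To detect a difference in change between randomization and 12 weeks of 1500 steps per day (SD 2824"), "given a two-sided 5% significance level, power of 80%, and an expected attrition of 23"%. Its result is that "a total of 148 participants (n=74 participants per group [57 plus 17 for attrition], and n=37 per recruitment center) is needed".

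The covariate list is carried over to the multivariate model for walking and moderate-to-vigorous energy expenditure. Table 2 also schedules baseline values for those two scores, for quality of life and for angina frequency.

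**The concern.** When the outcome is a change from baseline, the baseline value is usually related to that change: participants who start low tend to rise and those who start high tend to fall, through regression to the mean. A change score subtracts the whole baseline difference between arms (slope 1). Analysis of covariance subtracts only the part that the data support (the fitted slope). Unless the true slope is 1, the change score is the noisier estimator, and its estimate moves with any chance imbalance in baseline steps.

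At stake is the width of the confidence interval for the primary effect, in a trial designed at 80% power with 23% attrition expected. Naming the term in advance also matters because an open list would allow baseline adjustment to be added or left out after results are seen.

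**Working it through.** **Inputs from the protocol article.** Difference 1500 steps per day, SD 2824, two-sided 5%, power 80%, 57 evaluable per arm, 23% attrition, 1:1 allocation. **Not in the article, hence assumed:** the correlation r between baseline and 12-week steps, and the ratio k of the 12-week SD to the baseline SD.

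**1. The plan's own figure.** Standardized difference 1500/2824 = 0.531. A two-sample t test on change (noncentral t) needs 57 per arm, with power 80.3%. Attrition: 57/0.77 = 74.03, about 74 per arm, 148 in total. The stated size reproduces as a calculation for change without baseline adjustment.

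**2. What the stated model estimates.** If the repeated outcomes are the changes at 5 and 12 weeks, the model analyses change without a baseline term. If baseline steps is one of the repeated measures, then with complete data and covariates entered as main effects, the group-by-time contrast from baseline to 12 weeks equals the difference in mean change. If covariates interact with time, it is the covariate-adjusted change. None of these adjusts for baseline steps.

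**3. Gain from adding baseline, equal SDs (k=1).** With common SD s, the variance of change is 2s²(1−r) and the residual variance given baseline is s²(1−r²). The ratio is (1+r)/2, so the effective SD is 2824·√((1+r)/2). No credit is given for the seven other covariates.

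| r | variance ratio | effective SD | power at 57 per arm |
|---|---|---|---|
| no baseline term | 1 | 2824 | 80.3% |
| 0.3 | 0.65 | 2277 | 93.7% |
| 0.5 | 0.75 | 2446 | 90.1% |
| 0.7 | 0.85 | 2604 | 86.2% |
| 0.9 | 0.95 | 2752 | 82.2% |

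Simulation (4000 runs each) agrees: 80.5% against 89.6% at r=0.5, and 80.0% against 86.2% at r=0.7.

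**4. Unequal SDs (k=1.3, assumed).** The ratio becomes k²(1−r²)/(1+k²−2rk).
- r=0.5: 1.2675/1.39 = 0.912, power 83.7%.
- r=0.7: 0.8619/0.87 = 0.991, power 80.6%.

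The slope on baseline is rk: 0.65 at r=0.5, 0.91 at r=0.7 and 1.04 at r=0.8. Near 1, the change score loses almost nothing.

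**5. If 2824 is an SD at one time point (k=1).** The article says only: "The SD of 2824 steps per day was estimated using data found in an RCT of a counseling intervention in ACS patients in Quebec". It does not say whether that is an SD of change. On the single-time reading, the SD of change is 2824·√(2(1−r)) and the adjusted SD is 2824·√(1−r²). Power without and with baseline is 66.1% and 83.8% at r=0.3, 80.3% and 90.1% at r=0.5, and 95.2% and 97.6% at r=0.7. The direction is the same.

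**6. Sensitivity to chance imbalance (2824 as SD of change, k=1).** The baseline SD is 2824/√(2(1−r)). One standard error of the baseline difference is that SD times √(2/57). The change difference shifts by (1−r) times this.
- r=0.5: SD 2824, SE 529, shift 264 steps, 264/1500 = 18% of the target difference.
- r=0.7: SD 3646, SE 683, shift 205 steps, 205/1500 = 14%.

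This shift is one component of the sampling variance already counted in step 3.

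**The case against.** The strongest reply is that the list is open. This is a condensed article, the full model statement may sit in an analysis plan that is not shown, and no sentence excludes baseline steps. Statistical Methods also sorts dichotomous outcomes by whether they have baseline values, so the authors had baseline values in mind. That stands as a limit: a reader might infer that baseline adjustment was rejected, and the text does not support that. It does not remove the point. The article prints a specific list, names the baseline of another variable, and contains no baseline adjustment of steps in any form.

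Four stronger readings are tempting and should be resisted.
- That the trial analyses raw change. It does not: seven covariates are in the model and may recover some of the gain. How much cannot be computed from the article, so the powers above compare baseline adjustment with no adjustment at all.
- That a repeated measures model always reduces to the unadjusted change score. This needs complete data and main-effect covariates, and 23% attrition is expected.
- That power would rise to about 90%. That figure depends on an assumed correlation and on equal SDs. Baseline is measured from the third week after discharge, and the spread may differ by 12 weeks; with k=1.3 the gain nearly vanishes at r=0.7.
- That baseline imbalance adds a bias on top of lost precision. It is the same loss seen from another side.

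**Conclusion.** The point holds as one of efficiency. Outcome, sample size and model all concern change and do not contradict one another. Type I error, unbiasedness over randomization and the total of 148 are unaffected. What is lost is precision: in large samples, adjusting for baseline never gives a larger variance than the change score, and the planned baseline measurement allows it.

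Across the assumptions examined with 2824 as the SD of change, power at 57 per arm moves from 80.3% to somewhere between about 81% (r=0.7, k=1.3) and about 94% (r=0.3, k=1). The true correlation and SD ratio are not in the article, so no single figure should be quoted as the gain. The change is worth making because it is nearly free, not because the planned analysis is invalid.

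**What to change.** Name baseline steps per day as a covariate in the primary model. With baseline in the model, taking 12-week steps or change as the outcome gives the same treatment effect. Alternatively, specify a longitudinal model in which both arms share a common baseline mean; this can also retain participants with fewer than three valid baseline days. If an analysis plan already does either, say so in the protocol.

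Do the same with the matching baseline for each continuous outcome that has one: walking and moderate-to-vigorous energy expenditure, quality of life, and angina frequency. State this before the data are unblinded.

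The cost is one degree of freedom per model and no new data. The sample size need not change.
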